## Abstract

**Background:**

People living with HIV who are affected by substance use disorders and other social vulnerabilities are less likely to achieve and sustain viral suppression. Supporting these patients with mobile health systems can provide additional social and behavioral support that may improve HIV outcomes in these populations.

**Objective:**

This study aims to implement and evaluate an evidence-based digital health system (antiretroviral therapy care coordination; ART-C) to improve HIV viral suppression and reduce missed clinic visits within a multisite HIV care program.

**Methods:**

ART-C will be implemented in 8 HIV medical home clinics operated by Vivent Health in Colorado, Missouri, Texas, and Wisconsin. All patients receiving HIV care across the system will be invited to use a customized version of the Connections smartphone app to join a virtual community of peers living with HIV. A subset of patients with substance use disorder will be recruited to use enhanced features of the app, allowing sharing of information about substance use and other social determinants of health with their care team. Effectiveness and implementation outcomes will be evaluated using a stepped-wedge clinical trial design. Effectiveness will be evaluated by comparing missed visits and viral nonsuppression rates before and after the intervention. Implementation will be evaluated using a mixed methods approach based on the reach, effectiveness, adoption, implementation, and maintenance framework.

**Results:**

Funding was received April 2022 with data collection beginning December 6, 2023. Data collection is anticipated to end in 2027 with data analysis and results expected late 2027. As of submission of the manuscript, 86 participants were recruited. Of the 6710 patients with health record data available 2 years before the trial began, 1723 (25.68%) had a substance use disorder, 2825 (42.1%) missed at least 2 care visits, and 1354 (20.18%) had at least 1 detectable HIV RNA test (viral load ≥200 copies/mL), leaving 3816 (56.87%) eligible individuals. Analysis of preimplementation data demonstrated that patients had a mean of 4.1 (SD 2.1) to 7.8 (SD 5.5) care visits across all 8 Vivent Health sites, with 45% to 70% of patients missing at least 1 visit. Patients underwent a mean of 2.2 to 4 HIV RNA tests, and 14% to 37% of patients across clinics had at least 1 nonsuppressed HIV RNA result. Primary analyses are expected to be completed by 2028.

**Conclusions:**

This study will evaluate the effectiveness of and implementation strategies for a mobile health–based intervention to support patients with HIV, substance use disorder, and related challenges in engaging in care and achieving viral suppression.

**International Registered Report Identifier (IRRID):**

DERR1-10.2196/69842

## Introduction

### Background

Clinical implementation and global scale-up of antiretroviral therapy (ART) for HIV have transformed one of the deadliest pandemics in human history into a chronic disease management challenge. Before 2003, HIV and AIDS were a leading cause of death among young adults worldwide. In recent decades, however, effective treatment and systems of care have demonstrated such an impact that the World Health Organization has declared HIV elimination to be a realistic global health goal [1].

Elimination of HIV transmission through effective treatment (also referred to as “treatment as prevention”) can only be achieved through universal access to treatment and sustained viral suppression (defined as plasma HIV RNA levels that are lesser than the detection threshold of 200 copies/mL) for nearly all persons living with HIV [2]. Unfortunately, in the United States, only 62.7% of persons diagnosed with HIV infection had viral suppression in 2017 [3], a level that falls substantially short of the 95% goal set by the US Department of Health and Human Services for ending the epidemic [4].

Patients and communities impacted by substance use disorders (SUDs) and related social and behavioral vulnerabilities are significantly less likely to experience sustained HIV suppression [5-8]. In a cohort of people who inject drugs followed for a median of 8.7 years, only 30% were retained in care every year they were in the study [9]. Of those who reported receiving ART during the study, 86% achieved viral suppression during at least 1 study visit; however, only 12% were found to have achieved viral suppression at every study visit after ART initiation, meaning nearly 9 in 10 patients experienced virologic failure during their treatment [9].

Previous research has demonstrated that the determinants of suboptimal HIV treatment outcomes are heterogeneous and complex [10], suggesting that ending the HIV epidemic will require the implementation of multifaceted strategies to support vulnerable patients throughout their life course. Fortunately, systems of HIV care that address social determinants of health can help address these complex needs. Data from the Health Resources and Services Administration (HRSA) Ryan White HIV and AIDS Program (RWHAP) [11] showed that 85% of individuals who had at least 1 medical visit to a clinic funded by RWHAP during 2017 had achieved viral suppression [12]*.* A study on service delivery in RWHAP-funded facilities found that they were more likely to provide case management, mental health, substance use, and other support services compared to non–RWHAP-funded clinics, and patients attending these facilities were more likely to receive these services [13].

### The Need for Just in Time Strategies for Monitoring and Responding to Social Determinants of Health in HIV Care Settings

While clinical factors, such as antiretroviral adherence [14] and retention in care [15] are well understood to be proximal determinants of viral suppression, nonclinical factors, such as poverty [16], lack of health insurance [17], homelessness [18], food insecurity [19], and criminal justice involvement, also influence HIV care outcomes. In 1 community-based cohort study of predominantly African American people with HIV who inject drugs, participants who achieved viral suppression after initiating ART had a 1-in-4 risk of experiencing viral rebound (ie, virologic failure) during any 6-month interval [20]. In that study, loss of viral suppression was more common if participants reported recent incarceration, daily injection drug use, or homelessness, demonstrating how time-varying social and behavioral factors can signal vulnerability to treatment interruptions Other patient-level factors that have been consistently correlated with treatment interruptions include depression and anxiety [21], low self-efficacy, internalized HIV-related stigma [22], and inadequate social support [23].

A major challenge to addressing HIV-related health disparities is the tendency for patients to miss appointments during periods of greatest vulnerability. Research using electronic health record (EHR) data shows that treatment failure is predictable based on individual-level characteristics documented in the EHR [24,25]. However, the social, behavioral, and structural factors that increase the risk of treatment disruption and require the timely provision of support to ensure care retention are not typically captured in EHRs. Therefore, health care providers do not generally have timely access to data that would help them provide support when it is most needed. As a result, most disruptions in ART are detected only after a lapse in care has already occurred. The fact that previous treatment disengagement and virologic nonsuppression are 2 strong predictors of future care disengagement [24,25] further underscores the need to interrupt the cycle of treatment disruption and find new ways to support retention.

### Digital Health Approaches to Addressing Disparities in HIV Care

Real-time monitoring of patients with digital health systems can provide a platform to provide timely support and linkage to needed services. A suite of demonstration projects supported by HRSA’s Special Projects of National Significance explored the beneficial roles of social media and mobile health (mHealth) interventions, finding promise in three domains: (1) managing HIV care with subthemes of medical information accessibility, reminders, and self-efficacy; (2) fostering feelings of support and personal connectedness; and (3) helping alleviate negative feelings about status and mitigating HIV-related stigma [26]. Technology can empower patients with direct delivery of individualized motivation, education, and support [27]. Wireless technologies remove the barriers of time and distance between patients and health care providers; this is especially important for patients with SUD and other populations that are hard to reach and difficult to keep engaged in care. Digital health technology offers great potential for collecting higher-quality data related to care delivery and health outcomes, and facilitating more effective collaboration among HIV care providers.

In this paper, we describe a hybrid implementation effectiveness trial of a clinic-based intervention that seeks to leverage the numerous potential benefits of digital health strategies when deployed in the context of comprehensive, patient-centered HIV care. The approach described in the Methods section was informed by a pilot study funded by the National Institute on Drug Abuse, in which 200 people living with HIV were invited to use a digital health app, the Addiction–Comprehensive Health Enhancement Support System (CHESS), for a period of 2 years [28,29]. Lessons learned from the pilot study influenced the design of key intervention elements in this study, including the use of peer mentors to boost patient engagement with the digital health system and dedicated clinic case managers to act as liaisons between app engagement and the broader HIV care team.

## Methods

### Overview

The goal of this project is to implement and evaluate an evidence-based digital health system to improve HIV viral suppression and reduce missed clinic visits within a multisite, comprehensive HIV care program in the United States. Using a stepped-wedge, cluster randomized trial design, we will test the effectiveness of a care coordination intervention named ART-C (antiretroviral therapy care coordination). The intervention is a multicomponent strategy that combines medical case management; peer support; and the Connections app, which is a smartphone-based platform designed to support engagement in care for people living with SUD. After conducting formative research and a community-engaged protocol development process, the trial was approved by the institutional review board (IRB) in October 2023. Protocol version 4 was approved on November 14, 2024. In this paper, we discuss the intervention, study aims and methods, and the population eligible for recruitment into the clinic-supported arm of the study.

The Connections App (CHESS Health) is based on the CHESS, a mHealth system developed at the University of Wisconsin (UW). CHESS is a suite of secure, internet-based services delivered via smartphone that promotes positive behavior change and provides social support to people engaged in care for HIV, addiction, and other complex conditions. A randomized controlled study conducted in 2014 found that Addiction–CHESS, a derivation of CHESS designed for alcohol use disorder treatment, had a significant effect on treatment retention and reduced risky drinking behaviors [30].

When implemented in a multisite HIV care program operating under a patient-centered medical home model, we hypothesize that ART-C will improve care by supporting three needs: (1) facilitating real-time, community-based capture of data reflecting social and behavioral determinants known to precede lapses in HIV care (eg, housing and food insecurity, unhealthy alcohol or drug use, or poor medication adherence); (2) improving engagement in care by increasing social connectedness among patients and between patients and peer mentors; and (3) supporting retention in addiction treatment and mental health care that promote sustained engagement in HIV care.

### Study Aims

As a hybrid type 2 trial [31], the study has primary aims related to both effectiveness and implementation. The effectiveness-related aim of the study is to understand the impact of ART-C on the occurrence of virologic failure and missed clinic appointments among patients receiving HIV care. The implementation-related aim is to evaluate the deployment of ART-C within the HIV medical home model using the reach, effectiveness, adoption, implementation, and maintenance (RE-AIM) framework. We will analyze patient-, health care provider-, and clinic-level factors that influence the reach, effectiveness, implementation, adoption, and maintenance of ART-C within HIV care practices.

The hybrid trial design will simultaneously test the effectiveness of the ART-C intervention and the effect of a bundle of evidence-based implementation strategies. Our bundled implementation strategy is organized by the exploration, preparation, implementation, and sustainment framework [32]. The discrete implementation strategies that make up the bundle come from the Expert Recommendations for Implementing Change taxonomy [33].

### Study Design

The stepped-wedge design is a cluster-randomized, 1-way crossover study in which all units are initially assigned to the control condition, then switched to the intervention at randomly assigned time points until all units have crossed over by the last time interval. Stepped-wedge trials enable all sites to receive enhanced services while avoiding biases associated with uncontrolled pre- and poststudy designs. A site will be considered preintervention when it is in the control condition (before ART-C implementation), and postintervention after crossover. Primary outcomes will be passively collected using data from the health system’s EHR.

### Study Setting and Patient Population

ART-C will be implemented within 8 HIV medical home clinics operated by Vivent Health in Colorado, Missouri, Texas, and Wisconsin. The HIV medical home model provides HIV-oriented comprehensive care to people living with HIV and encompasses primary health care, dental care, mental and behavioral health services, case management, housing, prevention or harm reduction services, and food bank services.

To describe the baseline, preintervention occurrence of study outcomes, we defined a cross-sectional sample of active patients who would be eligible to receive ART-C as of December 2023. The baseline sample excluded patients who never attended a medical visit, died before the time of study approval, or did not speak English.

Demographic and clinical characteristics of the study sample were captured from the Vivent Health EHR (Epic Systems Corporation). The prevalence of SUD was determined based on visit diagnoses and problem list entries in the EHR, using the *International Classification of Diseases, 10th Revision,* codes (F10-16, F19, O35.4, O35.5, O99.31, and O99.32). Patients were also classified as having SUD if they were ever prescribed a medication to treat alcohol use disorder (acamprosate, disulfiram, topiramate, or naltrexone) or opioid use disorder (methadone, buprenorphine, or naltrexone). For medications that are used for the treatment of SUD and other conditions, patients were only considered to have SUD if the prescription order was paired with an appropriate diagnosis code for alcohol use disorder or opioid use disorder.

### Study Outcomes

We defined 2 study outcomes using EHR data, which will be examined at the clinic level and continually assessed during pre- and postimplementation periods. The first outcome, missed clinic visits, is defined as the proportion of appointments scheduled with an HIV care provider that a patient failed to attend and did not call in advance to cancel or reschedule. The second outcome, viral nonsuppression, is defined as the proportion of patients with an HIV RNA test result greater than the lower limit of detection (200 copies/mL) among those who received 1 or more HIV tests during the past 6 months.

These outcomes reflect the principle that optimal HIV care exists across a continuum, from timely diagnosis and linkage to care, to initiation of ART, and sustained adherence and retention in care over the life course [34]. They were selected because they have been identified as key quality improvement metrics by Vivent Health for all of its clinical sites. Missed visits are a marker of vulnerability for disengagement from care [35] and may predict loss of viral suppression [36] and subsequent mortality [37]. Viral suppression is the key indicator of a successful response to ART in all HIV care settings. Minimizing viral nonsuppression is, therefore, a main goal of national and global HIV elimination strategies [38].

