## Results

In the 2 years before starting ART-C implementation (December 2021 to November 2023), 6710 patients received HIV-related services, including a laboratory test or scheduled visit. After excluding patients who never attended a medical visit, died before the time of study approval, or did not speak English, the resulting sample included 6035 (89.94%) patients who received HIV care in 1 of the 8 participating clinics.

Demographic and clinical characteristics of patients in the baseline sample are provided in Table 1. The majority (75%-88%) of patients at all clinics described their gender as men. The mean age of the patients as of December 2021 ranged from 41.7 (Kansas City) to 48.7 years (Denver). Self-reported race varied geographically. African American and Black individuals comprised the majority of patients in the Milwaukee and St Louis clinics, while most patients in the other 6 clinics reported as White individuals. Hispanic ethnicity was least common in St Louis (60/1409, 4.26%) and most common in Austin (210/754, 27.9%). The prevalence of SUD among active patients ranged from 4.2% (13/307; Kansas City) to 37.4% (82/219; Kenosha).

Table 2 displays the results of the baseline analysis of the 2 main study outcomes, providing the baseline level of HIV care indicators to which future, postintervention results will be compared. Over the 2 years before trial inception, patients had a mean of 4.1 to 7.8 scheduled care visits across sites, and 45% to 70% of them missed 1 or more visits. Patients had an average of 2.2 to 4 HIV RNA tests, and 14% to 37% of them had at least 1 nonsuppressed (>200 copies/mL) HIV RNA test. Multimedia Appendix 1 provides additional patient characteristics, such as HIV transmission route, sexual orientation, employment, and other features of the patient population at the clinic.

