**HIV viral suppression outcomes**															
	HIV RNA tests completed, n	5017		4896		598		5552	2410	691		382		1147	
	Number of completed HIV RNA tests per patient, mean (SD)	3.3 (1.7)		2.7 (1.4)		3.1 (1.9)		2.2 (1.2)	2.1 (1.1)	3.4 (1.8)		4 (2)		3.2 (1.9)	
	HIV RNA tests that were nonsuppressed (%)	9.69		7.31		7.02		11.38	14.11	14.04		10.47		16.30	
	Patients with 1 or more non- suppressed HIV RNA tests (%)	21.65		16.86		13.91		27.05	30.65	26.09		15.73		37.18	

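### Viral nonsuppression is scored only among patients tested in the past 6 months, and ART-C may change who is tested, so the estimate can be biased toward no benefit

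*Protocol article*

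**What the plan says.** All references are to the protocol article.

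- **Numerator (Study Outcomes).** The outcome counts "the proportion of patients with an HIV RNA test result greater than the lower limit of detection (200 copies/mL". The text does not say whether any, the last or the worst result is used when a patient has several.
- **Denominator (Study Outcomes).** It is limited to those tested: "among those who received 1 or more HIV tests during the past 6 months". Untested patients are outside the outcome.
- **Purpose of ART-C (Overview).** The aim is to "improve HIV viral suppression and reduce missed clinic visits".
- **Rationale (The Need for Just in Time Strategies).** The article points to "the tendency for patients to miss appointments during periods of greatest vulnerability". Study Outcomes adds that missed visits may predict loss of suppression.
- **Baseline (Results, Table 2).** "Patients had an average of 2.2 to 4 HIV RNA tests" over two years, and "14% to 37% of them had at least 1 nonsuppressed" result. Results presents Table 2 as the level against which post-intervention results will be compared.
- **Model (Analytic Strategy: Effectiveness and Maintenance).** It has site, time and intervention status, with covariates, interactions and unspecified weighting methods to be added later. None of these is tied to whether a patient was tested.

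**The concern.** The denominator depends on an event that occurs after crossover and that the intervention may alter. Viral load testing plausibly follows attendance, and attendance is the other primary outcome. A patient who would have skipped a visit and its laboratory test in a control period is absent from the outcome. The same patient, kept in contact by ART-C, is tested and counted. On the article's own rationale, such patients are more likely to be viremic.

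Success on missed visits could therefore raise measured nonsuppression without anyone's viral load worsening. A secular time effect does not absorb this, because the change in composition coincides with the intervention indicator. At stake are a diluted effect, lost power and, in unfavourable cases, the wrong sign.

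The unspecified counting rule could push in the same direction: if any nonsuppressed result counts, a patient tested twice has two chances to be scored nonsuppressed.

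**Working it through.** **1. The plan's own power.** Inputs from the power paragraph: 26.7% falling to 16.7%, 3682 patients, design effect 3.0. Two-sided alpha of 0.05 is assumed, as none is stated. Effective number per condition = 3682 / 3.0 / 2 = 613.7. A two-proportion calculation gives 98.9% power (stated: 98.5%), and 82.9% for a 7-point fall (stated: above 80%). Both reproduce.

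**2. How many patients are untested in a 6-month window?** Table 2 does not settle this.
- Tests sum to 20,693 and clinic sizes to 6032. 20,693 / 6032 / 4 = 0.86 tests per patient per window, which would leave at least 14% untested.
- That divisor is everyone seen at any time in 24 months. On the 4208 active patients in the power paragraph, 20,693 / 4208 / 4 = 1.23, which gives no lower bound.
- Table 2's rows also disagree. Madison: 382 / 170 = 2.25 tests per patient against a printed mean of 4. St Louis: 5552 / 1409 = 3.94 against 2.2.

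The 14% is used below only as an assumption.

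**3. Illustrative clinic, no true effect.** 526 patients (the stated average per site), 452 tested and 74 untested (14%), with 26.7% nonsuppressed among the tested: 0.267 × 452 = 120.7. Assume half of those newly tested are viremic.
- Half of the untested return (37): (120.7 + 18.5) / (452 + 37) = 28.5%, or **+1.8 points**.
- A quarter return (18.5): (120.7 + 9.25) / (452 + 18.5) = 27.6%, or **+0.9 points**.

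The base rate matters. Starting from 10.5%, the weighted share of *tests* nonsuppressed in Table 2, the first case would show 66 / 489 = 13.5%, or +3.0 points. But the outcome is a proportion of patients, so 26.7% is the better base.

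**4. General form.** Let x be the share of the post-crossover denominator that is newly tested and u their nonsuppression rate; the article gives neither. Observed rate = (1 − x) × p + x × u, where p is the rate in those already tested. The shift with no true effect is x × (u − 0.267). The sign reverses under the planned effect when x exceeds 0.10 / (u − 0.167).

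| u | Shift, no effect, x = 5% | Shift, no effect, x = 10% | Observed rate, true fall to 16.7%, x = 10% | Power, x = 10% | Sign reverses at x above |
|---|---|---|---|---|---|
| 40% | +0.7 | +1.3 | 19.0% | 89% | 43% |
| 60% | +1.7 | +3.3 | 21.0% | 64% | 23% |
| 100% | +3.7 | +7.3 | 25.0% | 10% | 12% |

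The larger illustration in step 3 has x = 37 / 489 = 7.6% and u = 50%. With the planned effect the observed rate is 0.924 × 0.167 + 0.076 × 0.50 = 19.2%. That is a 7.5-point fall instead of 10, with about 88% power.

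**5. Counting rule.** At a per-test rate of 10% and independent results (an upper-end assumption), one test gives 10% ever nonsuppressed and two give 1 − 0.9² = 19%. Correlated results would give a smaller rise.

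**6. Counting untested patients as not documented suppressed.** Same clinic, no viral load changed. Before: (120.7 + 74) / 526 = 37.0%. After half return: (120.7 + 18.5 + 37) / 526 = 33.5%. The rate falls 3.5 points through testing alone.

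**The case against.** **Reversal is not shown.** A reader might infer that a beneficial ART-C will look harmful. The documents do not support that. At the planned effect the sign reverses only if 12% to 43% of the post-crossover denominator is newly tested, depending on u. This stands: dilution is the likelier result.

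**The direction is not assured.** The stated mechanisms are mostly about preventing lapses, and a retained patient who stays suppressed adds a suppressed result. Re-engaged patients may also resuppress by a later window. Nothing equates being untested for 6 months with being viremic. This stands, which is why the bias is conditional on newly tested patients being worse than those already tested.

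**Few lapsed patients can be reached.** The clinic-supported arm requires current care at Vivent Health, and planned reach is 15%, about 79 of 526 patients. Thirty-seven returners would be nearly half of those. This limits the size. It does not remove the problem, because the bias needs only skipped visits and tests, not full disengagement, and the app is offered to every client.

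**The counting rule may be settled elsewhere.** A reader might take the definition to mean that any nonsuppressed result counts. Study Outcomes does not fix this, and the full protocol may. Table 2's rule of one or more supports the reading but describes 24 months.

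**The measure is deliberate.** It is a quality metric of the health system, and replacing it with one that counts untested patients as failures would let testing alone favour ART-C (step 6). This stands against changing the primary outcome, but not against the additions below.

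**Conclusion.** The point holds in a limited form. The tested-only denominator depends on a post-crossover event that ART-C may change, and no safeguard tied to testing appears in the article. If newly tested patients are more often viremic than those already tested, the estimate is biased toward no benefit and possibly toward apparent harm.

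The size is unknown. In the illustrated clinic it is about +1 to +2 points at the plan's 26.7% rate. That rests on assumptions the article does not supply: 14% untested, a quarter to a half of them returning, and half of those viremic. Neither 14% nor Madison's apparent 44% (1 − 382 / 170 / 4) is a firm floor. An any-result rule, if used, would add a second upward bias.

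**What to change.** 1. Keep the tested-only outcome as primary, but score one result per patient per period: the last HIV RNA. This removes the dependence on number of tests.
2. Analyse the proportion of active patients tested, by condition, with the same model, and report it beside the primary result. A difference tells the reader that the denominator has shifted.
3. Prespecify a sensitivity analysis on all patients active at the start of each period, with untested patients counted as not documented suppressed. State that this version can favour ART-C through testing alone, so that it is read together with the primary.

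The cost is a revised outcome wording and a little more analysis from the same EHR extract. The sensitivity version will show higher levels than the health system's usual metric, and some patients counted as not documented suppressed will in truth be suppressed.
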